## Aims and hypotheses

2

The current study (NCT06264154) has two aims. Aim 1 seeks to evaluate the effects of fruit-flavored versus tobacco-flavored and menthol-flavored e-cigarettes on combustible cigarette smoking among adults who have persistently smoked. We hypothesize that participants randomized to fruit-flavored e-cigarettes will be more likely to switch from combustible cigarettes to e-cigarettes during the 6-week switch phase and at the 26-week follow-up than participants randomized to tobacco-flavored or menthol-flavored e-cigarettes. Complete switching, partial switching, and no switching will be measured. Aim 2 seeks to examine whether the rewarding and reinforcing effects of e-cigarette flavoring mediate switching behavior. We hypothesize that fruit-flavored e-cigarettes will produce greater subjective reward, relative reinforcing value, and positive affect than tobacco-flavored or menthol-flavored e-cigarettes. In turn, greater subjective reward, relative reinforcing value, and positive affect will predict fewer cigarettes smoked per day during the 6-week switch phase and at the 26-week follow-up.

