#### Sample size

3.10.1

For Aim 1, hypotheses will be tested with 80% power using 5% two-sided alpha Bonferroni corrected to 2.5% for two group comparisons. The primary outcome is the longitudinal daily cigarette count from baseline (days 1-5) to the end of the e-cigarette switch phase (day 49), with week 26 as a secondary endpoint. We based the power on data from prior switching studies. A sample of 210 (70 per group) will allow us to detect an overall standardized slope of 0.19. To account for a ∼15% attrition rate [67], we will enroll ∼ 240 participants to have 210 who complete the 26-week follow-up. We expect the initial and sustained switch for participants randomized to fruit-flavoring to be greater than for participants randomized to tobacco or menthol flavoring. A sample of 70 per group enables us to detect a difference of ∼3.73 cigarettes per day (CPD). We will also be able to detect a difference in slopes of 0.13 (CPD per day change).

For Aim 2, a sample of 70 per group will allow us to detect a between-group effect size of 0.5. For the relative reinforcing value of flavored e-cigarettes (RRVF), this means we can detect a difference in breakpoint of 2.0. Positive affect will be assessed as a difference score with a standard deviation of approximately 7.0, yielding 80% power to detect a difference of approximately 3.7. Subjective reward has a standard deviation of 1.3, which allows us to detect a 0.68 difference. In turn, the continuous measures of RRVF, positive affect, and subjective reward will be used to predict changes in mean cigarette counts from baseline to the end of the switch phase and from baseline to the 26-week follow-up. The sample of 210 allows us to detect a standardized slope of 0.2. The actual standard deviation for the cigarette consumption change score is 7.1. The detectable slopes are 0.37 for RRVF, 0.20 for positive affect, and 1.07 for subjective reward.

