#### Data analysis

3.10.2

Prior to analyses, the data will be screened for entry errors and outliers, the extent and type of missing data will be assessed, and the most appropriate method for dealing with the missing data will be selected. For Aim 1, longitudinal cigarette counts (normalized as percent of baseline) will be analyzed using mixed models (Gaussian family) in the primary analysis. The model will include predictors of time (continuous or discrete), study phase (baseline, switch period, or follow-up), flavor group, candidate covariates, and predictors (e.g., e-cigarette use). It will be tested using the z-scores corresponding to the study phase by flavor group interaction terms with fruit-flavored as the reference. For an intent-to-treat (ITT) analyses, ITT will be defined as those randomized to a flavor group at day 6.

For Aim 2, measures are summary scores and difference scores and will be addressed using multiple regression methods. We will first test whether participants randomized to fruit versus tobacco or menthol-flavored e-cigarettes report greater subjective reward, greater increases in positive affect, and have a higher relative reinforcing value of e-cigarette flavoring using the t-score associated with the group difference. We will then test whether these effects predict fewer cigarettes smoked per day during the 6-week switching phase and at the 26-week follow-up.

Next, we will evaluate whether subjective reward, positive affect, and relative reinforcing value for entry into a model as predictors of change in cigarettes smoked per day (mean switch phase or follow-up cigarettes minus mean baseline cigarettes), using the significance of the corresponding t-score while controlling for craving, withdrawal, and negative affect relief. The series of regressions will occur within a structural equation model, with the effects of flavor (predictor) on cigarettes per day (outcome) across the switch follow-up phases mediated by subjective reward, positive affect, and the relative reinforcing value of flavor. We will compute the proportion of mediation for the indirect effects and evaluate the mediated paths for significance using the delta method and bootstrapped standard errors [[68], [69], [70]].

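### The Aim 2 text can be read as admitting the three pre-specified mediators by their own significance, which conflicts with adjacent text and, if applied, overstates the mediators that are kept

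*Protocol article*

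**What the plan says.** Protocol article, section 3.10.2 (Data analysis), Aim 2:

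- Flavor groups are first compared on the three mediators. A test then follows of whether those effects predict smoking.
- A further step evaluates "subjective reward, positive affect, and relative reinforcing value for entry into a model as predictors of change in cigarettes smoked per day". The criterion is stated as "using the significance of the corresponding t-score while controlling for craving, withdrawal, and negative affect relief". The opening clause of this sentence lacks a verb. No threshold is given, and nothing says what happens to a mediator that fails.
- The next sentence places the regressions in a structural equation model, with the flavor effect "mediated by subjective reward, positive affect, and the relative reinforcing value of flavor". It attaches no condition to that list.
- The plan will compute the proportion mediated and "evaluate the mediated paths for significance using the delta method and bootstrapped standard errors".

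Section 2 (Aims and hypotheses) states in advance that "greater subjective reward, relative reinforcing value, and positive affect will predict fewer cigarettes smoked per day", and Table 1 lists the same three measures as the mediating variables. Section 3.10.1 (Sample size) gives the planning value: "The sample of 210 allows us to detect a standardized slope of 0.2".

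**The concern.** Entry into a model decided by the significance of a t-score is variable selection. If the mediated paths are then estimated on the same people, three things follow. A slope kept because it was significant is biased away from zero. A true mediator that misses the cut passes part of its effect to the correlated mediators that stayed. The paths that failed go unreported. None of this is needed here, because the three mediators are already fixed by hypothesis.

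At stake is the trial's explanation of why flavor affects switching, which the conclusions (section 4.2) present as a main product of the study. Under an entry rule, the mechanism named would depend partly on which slope happened to pass. The primary outcome is not affected.

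**Working it through.** **1. Reproduce the plan's Aim 2 figures.** Inputs from section 3.10.1: N = 210, 80% power, SD of change in cigarettes 7.1, SD of subjective reward 1.3, SD of positive affect change 7.0.

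- Detectable correlation at two-sided 5%: tanh((1.960 + 0.842)/√207) = 0.192. Per residual SD: 0.192/√(1 − 0.192²) = 0.196.
- Subjective reward: 0.196 × 7.1/1.3 = 1.07. Positive affect: 0.196 × 7.1/7.0 = 0.20. Both match the plan: "The detectable slopes are 0.37 for RRVF, 0.20 for positive affect, and 1.07 for subjective reward".
- Group difference at 2.5%: (2.241 + 0.842) × √(2/70) = 0.521 SD, so 0.521 × 1.3 = 0.68 for subjective reward and 0.521 × 7.0 = 3.65 for positive affect (stated as 0.68 and about 3.7).

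The planning slope of 0.2 is therefore sound for one mediator at a time, and it is used below.

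**2. Set the sentences side by side.** If entry depends on significance, the sentence that names all three mediators in the structural equation model is not generally true. If all three always stay, the words on entry do nothing. Both cannot stand as written.

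**3. Hand check of the bias, uncorrelated measures.** In simulation (step 4) each true mediator at slope 0.2 passes |t| > 1.96 in 81% of trials.

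- The expected t is then 1.96 + 0.878 = 2.838.
- All three pass in 0.81³ = 53% of trials.
- The mean of a kept t is 2.838 + φ(0.878)/0.81 = 2.838 + 0.335 = 3.173, an overstatement of 3.173/2.838 = 1.12.
- At half the slope the expected t is 1.419 and the pass rate is 29%. The overstatement is (1.419 + φ(0.541)/0.294)/1.419 = 1.83.

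**4. Simulation.** N = 210 in three arms. Each mediator is shifted 0.526 SD in the fruit arm (close to the 0.521 above). Outcome = slope × mediators + direct effect + residual of SD 1, with total flavor effect 0.526 SD. Entry requires |t| > 1.96 in a regression on flavor, three mediators and three relief scores; the model is then refitted with those kept (3,000 runs per setting). The correlations and the 5% entry level are assumptions, because the document gives neither.

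| True slope | Correlation among mediators / with relief scores | All three enter | At least one left out | Kept slope ÷ truth | Coverage of slope interval |
|---|---|---|---|---|---|
| 0.20 | 0 / 0 | 53% | 47% | 1.11 | 97% |
| 0.20 | 0.3 / 0.2 | 36% | 64% | 1.23 | 94% |
| 0.20 | 0.5 / 0.3 | 18% | 82% | 1.42 | 85% |
| 0.15 | 0 / 0 | 17% | 83% | 1.32 | 96% |
| 0.15 | 0.3 / 0.2 | 7% | 93% | 1.55 | 87% |
| 0.15 | 0.5 / 0.3 | 2% | 98% | 1.85 | 67% |
| 0.10 | 0 / 0 | 3% | 97% | 1.81 | 92% |
| 0.10 | 0.3 / 0.2 | about 0% | about 100% | 2.18 | 76% |
| 0.10 | 0.5 / 0.3 | about 0% | about 100% | 2.52 | 48% |

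A separate set of runs used a flavor effect of 0.5 SD and correlations of 0 to 0.5. It gave milder results in the same direction. At slope 0.20 and a 5% rule, at least one mediator was left out in 39% to 71% of trials, overstatement was 1.09 to 1.27 and slope coverage 97% to 93%. At a 2.5% rule the figures were 54% to 83%, 1.12 to 1.36 and 97% to 91%.

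**5. The indirect effect, which is what the plan tests.** At slope 0.2 a kept indirect effect is overstated about 1.1 to 1.4 times, like the slope. Its delta-method interval nevertheless covers 98%, 97% and 95% at the three correlation settings, because the interval also carries the uncertainty of the flavor-to-mediator path, which is not selected. At slope 0.10 coverage is 98%, 93% and 82%.

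**6. Comparison: all three entered regardless.** The mean slope equals the true value (0.20, 0.15, 0.10). Slope coverage is about 95%, and delta-method coverage at slope 0.2 is about 93%. That small shortfall is unrelated to selection.

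**The case against.** The strongest reply is that no entry rule is actually stated. The sentence is broken and gives no threshold. Elsewhere the same section uses t-scores and z-scores to describe ordinary hypothesis tests, so this one may only announce a test of the mediator-to-outcome path, which section 2 hypothesizes. The next sentence then keeps all three mediators, which is what the fix asks for.

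This stands in part. Entry only if significant is the natural reading but not the only one, and a reader who takes it as the settled rule goes beyond the text. On the benign reading, however, the words on entry serve no purpose, and the preceding paragraph has already announced the test of prediction. The wording needs repair either way.

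Three further points are fair:

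- A reader might infer that intervals computed after selection no longer cover. That does not hold at the planned slope for the quantity the plan tests (step 5). Clear loss of coverage needs weaker slopes together with correlated measures, or strong correlation in the case of the slope itself.
- A reader might infer that the fix would let the trial establish more mechanisms. It would not. The t-statistics in the full model are the same ones used for entry, so all three paths would be significant in the same share of trials.
- A single mediator at slope 0.2 is lost in about 15% to 37% of trials across the two sets of runs. It is the loss of at least one of three that is common.

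The exact threshold, and whether the bootstrap would repeat an entry step, are details an article may leave to the analysis plan. They are not counted here.

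**Conclusion.** The point holds as a conflict in the text with a conditional consequence. Section 3.10.2 can naturally be read as admitting mediators by significance in the trial's own data, against its own next sentence, section 2 and Table 1.

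If it is applied that way at 5% and the planned slope of 0.2, at least one true mediator is left out in roughly 40% to 80% of trials. Kept slopes and indirect effects are overstated about 1.1 to 1.4 times, and 1.8 to 2.5 times at half that slope. At slope 0.2, coverage is 97% down to 85% for slopes and 95% to 98% for indirect effects, so coverage is not the main harm.

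The direction of the bias is the same in every setting run with non-zero slopes. Its size rests on the assumed correlations (0 to 0.5), the assumed entry level, and all three mediators being real and equally strong. The matter concerns Aim 2 only.

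**What to change.** Delete the wording on entry by significance. State instead, for example: *Subjective reward, positive affect and relative reinforcing value are entered together in one pre-specified structural equation model for each outcome period (switch phase; 26-week follow-up), whatever their individual p-values. Every indirect effect is reported with its interval. The t-tests serve only as tests of the mediator-to-outcome paths.*

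The cost is one sentence and no extra data. The small downside is slightly wider intervals if one mediator is truly null. The gain is unbiased paths, complete reporting and an end to the contradiction, with no change in the power to declare each path significant.

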#### Flavor-associated subjective reward and positive affect (Day 6)

3.5.1

Participants will attend a laboratory session after overnight smoking abstinence (10 h; CO verified <10) on day 6 [23,34]. Cigarette craving, withdrawal symptoms, and positive and negative affect will be measured before e-cigarette exposure. They will receive instructions on how to use the e-cigarette before two e-cigarette exposures based on their flavor group assignment. On day 6, the traditional flavor groups will receive either two exposures of tobacco or two exposures of menthol flavoring, depending on their assignment. The fruit flavor group will receive blueberry and watermelon in a counterbalanced order. All exposures will have the same characteristics, only differing by flavor. Participants will take 14 puffs for the first exposure and 14 puffs for the second exposure. The exposures will be separated by 45 min [23,35]. After each exposure, participants will complete measures of subjective reward, craving, withdrawal, and affect. We chose to offer both watermelon and blueberry to participants randomized to fruit-flavored e-cigarettes to promote adherence if either flavor was unappealing. After this 1.25-h visit, participants will be compensated $40.

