**Baseline Covariates**					
Demographics	X				
Smoking History	X				
E-cigarette History	X				
Nicotine Dependence	X			X	X
Cigarettes per day (days 1-5)	X				
Depression & Anxiety	X				
CO	X	X	X	XXXXXX	X

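### The Aim 2 outcome model does not enter baseline cigarettes per day, and it conditions on relief scores taken after flavour exposure without defining the denominator of the proportion mediated

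*Protocol article*

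**What the plan says.** Section 3.10.2 (Data analysis) of the protocol article sets the Aim 2 outcome as a raw change score: "mean switch phase or follow-up cigarettes minus mean baseline cigarettes". Subjective reward, positive affect and relative reinforcing value (RRVF) are tested as predictors of that change, "using the significance of the corresponding t-score while controlling for craving, withdrawal, and negative affect relief". No other control is named for this model. The regressions then sit inside a structural equation model (SEM), and the plan adds: "We will compute the proportion of mediation for the indirect effects". It does not say what that proportion is a proportion of.

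Section 3.5.1 gives the timing of the relief measures on day 6. Before vaping: "Cigarette craving, withdrawal symptoms, and positive and negative affect will be measured before e-cigarette exposure". Afterwards: "After each exposure, participants will complete measures of subjective reward, craving, withdrawal, and affect". Each relief score therefore uses a reading taken after exposure to the randomised flavour, at the same sitting as reward and affect.

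Table 1 lists CPD on days 1-5 among the baseline covariates, and section 3.8 gives a general covariate list. Neither is assigned to a model. Table 1 classes the relief scores as predictors, apart from the mediators. The Discussion presents the adjustment for negative reinforcement as intended.

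**The concern.** Randomisation balances baseline CPD across flavours. It therefore protects the total flavour effect and the flavour-to-mediator path. It does not protect the mediator-to-CPD slope, because nobody is randomised to a level of reward, affect or RRVF.

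A participant who switches completely has a change score of exactly minus baseline. Change therefore depends on baseline CPD unless post-baseline smoking rises one for one with baseline. A mediator that tracks heaviness of smoking can then appear to predict change with no effect of its own. For Aim 1 the same section scales the counts to baseline; the Aim 2 text makes no such provision.

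The relief scores raise a second question. Flavour may change relief. If so, conditioning on relief takes that route out of the modelled flavour effect, and a proportion mediated computed from what remains differs from a proportion of the randomised effect. Mechanism is one of the trial's two aims, so both points bear on a conclusion that the trial intends to draw.

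**Working it through.** **1. The plan's own figure (section 3.10.1).** Inputs are N = 210, 80% power and change-score SD 7.1. The detectable standardised slope is tanh[(z_alpha + z_power)/√(N − 3)].

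- Two-sided 5%: tanh[(1.960 + 0.842)/√207] = 0.192.
- Two-sided 2.5%: tanh[(2.241 + 0.842)/√207] = 0.211.

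The stated 0.2 lies between them. Raw slopes are 0.2 × 7.1/SD of the mediator:

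- Positive affect: 0.2 × 7.1/7.0 = 0.203 (stated 0.20).
- Subjective reward: 0.2 × 7.1/1.3 = 1.09 (stated 1.07).
- RRVF: 0.2 × 7.1/4.0 = 0.355, with SD 2.0/0.5 = 4.0 (stated 0.37; SD 2.0/0.525 = 3.81 gives 0.373).

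These figures reproduce to rounding and are not in dispute.

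**2. Omitting baseline CPD.** Let B be baseline CPD and let post-baseline CPD be βB + error. Change is then (β − 1)B + error. A mediator with no effect of its own, correlated r with B, has the expected standardised slope

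r × (β − 1) × SD_B/7.1.

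The documents do not give SD_B, β or r. Assumed: SD_B = 6, β = 0.3 to 0.7, r = 0.1 to 0.3. The two extremes are:

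- r = 0.1, β = 0.7: 0.1 × (−0.3) × 6/7.1 = −0.025.
- r = 0.3, β = 0.3: 0.3 × (−0.7) × 6/7.1 = −0.177.

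Simulation (N = 210, 2,000 runs per cell, two-sided 5% test, flavour group in the model, true mediator slope 0). Each cell gives the formula slope and the rejection rate without baseline:

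| β | r = 0.1 | r = 0.2 | r = 0.3 |
|---|---|---|---|
| 0.3 | −0.059, 14% | −0.118, 40% | −0.177, 73% |
| 0.5 | −0.042, 10% | −0.085, 23% | −0.127, 43% |
| 0.7 | −0.025, 7% | −0.051, 11% | −0.076, 19% |

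With baseline entered, rejection in these nine cells is 4.6% to 6.0%. With r = 0 or β = 1, rejection without baseline is 4.3% to 5.8%, so there is no bias. The simulation leaves out the relief scores; if they correlate with baseline CPD, they would take up part of the bias.

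Entering baseline also gains precision. The residual SD is √(7.1² − [(1 − β) × 6]²): √(50.41 − 17.64) = 5.7 at β = 0.3 and √(50.41 − 3.24) = 6.9 at β = 0.7, against 7.1.

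**3. Direction.** The hypothesis for reward and positive affect is a negative slope on change, so a positive r pushes towards it and a negative r against it. For RRVF, section 3.5.2 defines the breakpoint so that a higher value means stronger reinforcement from cigarettes. If heavier smokers have higher breakpoints, the bias runs against the hypothesis.

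**4. Conditioning on relief.** These are large-sample linear models (400,000 subjects) with assumed path values. Here a is the flavour-to-mediator path, b the mediator slope and c′ the remaining flavour effect.

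- *Relief not changed by flavour or mediator.* The share mediated is 0.50 with or without relief.
- *Relief a parallel route* (a = 0.5, b = −0.2; relief path 0.5 × −0.2; direct −0.1). The total is −0.1 − 0.1 − 0.1 = −0.3. The slope stays right at −0.20. The share of the total is 0.1/0.3 = 0.33, but ab/(ab + c′) = 0.1/0.2 = 0.50.
- *Relief downstream of the mediator.* The slope falls from −0.20 to −0.10. The share falls from 0.50 to 0.24 (of the total) or 0.33 (of ab + c′).
- *Relief and mediator share a cause, and relief affects CPD.* Leaving relief out gives −0.30 against a true −0.20; including it gives −0.20.
- *Relief a collider.* A true slope of 0 becomes +0.14.

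**The case against.** The best defence is that this is a condensed article. A full covariate list is commonly left to the analysis plan, Table 1 already names baseline CPD as a covariate, and naming the relief scores as controls does not say that nothing else enters. The sentence on the SEM also gives its outcome as CPD rather than change, so the change score may not run through every equation. This stands as far as it goes: a reader might infer that the trial will ignore baseline CPD, and the documents do not say so. They do fix a change score and name a control set for it, and baseline CPD is not in that set.

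A reader might also infer that mediation could be declared purely because heavier smokers find vaping more rewarding. That does not follow. An indirect effect also needs flavour to move the mediator, and randomisation protects that path. Nor do the documents show that heavier smokers score higher on reward. Stratification by nicotine dependence does not answer the narrower point, because it balances the groups and leaves the mediator-CPD association as it is.

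A third tempting reading is that adjusting for relief is wrong, or that the proportion mediated will be overstated. The Discussion shows that the adjustment is deliberate, to separate positive from negative reinforcement. Depending on the causal structure it can raise the proportion, lower it, leave it alone or remove confounding.

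**Conclusion.** The point holds as a specification fault in the Aim 2 outcome model. As written, the model leaves the mediator-to-CPD slope open to confounding by baseline CPD. Under the assumed inputs the false standardised slope is -0.03 to -0.18, close to the plan's detectable 0.2 at the upper end. False rejection is 7% to 73%. Both figures depend on a mediator-baseline correlation and a post-baseline-on-baseline slope below 1; if either is absent, so is the bias.

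The proportion mediated is not interpretable as written. Its denominator is undefined, and the model conditions on scores that flavour may change; the direction of any distortion cannot be known from the documents.

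The Aim 1 primary analysis and the sample size are untouched. No fault is shown in using a difference score for positive affect. The change is worth making, but it concerns secondary mediation results only.

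**What to change.** 1. Enter baseline mean CPD (days 1-5) as a covariate in every Aim 2 outcome equation, for the switch phase and for week 26. Modelling post-baseline mean CPD adjusted for baseline is equivalent: the mediator slope is the same.
2. Keep the craving, withdrawal and negative-affect relief scores, but give them their own flavour paths as parallel mediators, or report the model with and without them. Reward and relief are measured at one sitting, so the data cannot settle their causal order; the paired report shows how far the result depends on it.
3. Define the denominator of the proportion mediated as the total randomised flavour effect.

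The cost is one covariate that is already collected and a few more SEM paths. No new data and no change in sample size are needed.

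### Testing the Aim 2 indirect effects with delta-method and bootstrapped standard errors gives up about 30% (5% alpha) to 45-50% (2.5% alpha) of the power a percentile bootstrap interval would have at the trial's own detectable effects

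*Protocol article*

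**What the plan says.** Section 3.10.2 of the protocol article (Data analysis) places the Aim 2 regressions in a structural equation model in which the effect of flavor on cigarettes per day is "mediated by subjective reward, positive affect, and the relative reinforcing value of flavor". The significance rule for the indirect effects is to "evaluate the mediated paths for significance using the delta method and bootstrapped standard errors". No bootstrap confidence interval is named. The same sentence adds: "We will compute the proportion of mediation for the indirect effects".

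Before that step, the section tests each link separately: flavor on each mediator, and each mediator on change in cigarettes per day, both by t-score.

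Section 3.10.1 (Sample size) gives detectable effects for the two links but no power for their product. For flavor to mediator, "a sample of 70 per group will allow us to detect a between-group effect size of 0.5". For mediator to outcome, "The sample of 210 allows us to detect a standardized slope of 0.2". The only alpha stated is introduced for Aim 1: "hypotheses will be tested with 80% power using 5% two-sided alpha Bonferroni corrected to 2.5% for two group comparisons".

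**The concern.** An indirect effect is the product of two estimated coefficients, a (flavor to mediator) and b (mediator to outcome). Unless both are large relative to their standard errors, the product has a skewed distribution and a normal reference curve fits it poorly. The delta method uses that curve directly. A bootstrapped standard error replaces only the denominator; the ratio is still compared with a normal critical value, so the conservatism stays.

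At stake is the formal mediation test of Aim 2. It may often miss significance even when both links exist at the sizes for which the trial was planned, although the bootstrap resamples it already intends to draw would support a more powerful test.

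**Working it through.** **1. Reproduce the plan's figures.** Inputs from section 3.10.1: 70 per group, 210 in total, 80% power.

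- Flavor to mediator: d = (z for alpha/2 + z for 80% power) × √(2/70).
  - At two-sided 2.5%: (2.241 + 0.842) × 0.169 = 0.521. On SD 1.3 this is 0.677, and on SD 7.0 it is 3.65.
  - The plan states: "Subjective reward has a standard deviation of 1.3, which allows us to detect a 0.68 difference", and for positive affect "yielding 80% power to detect a difference of approximately 3.7". Both match.
  - At 5%, d would be 0.474. The rounded d = 0.5 has 76% power at 2.5% and 84% at 5%.
- Mediator to outcome: slope = (sum of the same z values) / √210. This gives 0.193 at 5% and 0.213 at 2.5%; the plan states 0.2.
- The stated raw slopes, standardized with the outcome SD of 7.1, agree: 1.07 × 1.3/7.1 = 0.196 (subjective reward), 0.20 × 7.0/7.1 = 0.197 (positive affect), and 0.37 × 4.0/7.1 = 0.208 (relative reinforcing value, assuming SD 4.0 = 2.0/0.5).

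The group-difference figures imply 2.5% and the slope lies between the two levels. Both alphas are therefore carried forward.

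**2. Why the stated tests are conservative.** With path statistics z_a and z_b, the first-order delta statistic is z_a·z_b / √(z_a² + z_b²), which is always smaller than the weaker of the two.

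- z_a = 0.5/√(2/70) = 2.96.
- z_b = 0.2 × √210 / √(1 − 0.2²) = 2.96.
- Delta statistic = 2.96/√2 = 2.09.

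The critical values are 1.96 (5%) and 2.24 (2.5%). An expected value this close to the cut-off means power near one half at 5%, and less at 2.5%.

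**3. Simulation.** Three arms, two dummy variables with fruit as reference, fruit versus one comparator, normal errors, complete data, no direct effect. There were 2,004 trials per scenario and 1,000 resamples per trial; Monte Carlo error is about 1.1 points. All three methods were applied to the same data. Relative loss = 1 − (power of the stated test / power of the percentile interval), shown for the delta method and then the bootstrapped SE.

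| Scenario | Alpha | Delta | Bootstrapped SE | Percentile interval | Relative loss |
|---|---|---|---|---|---|
| d 0.5, slope 0.2, 70 per arm | 5% | 48.3% | 45.4% | 67.2% | 28%, 32% |
| | 2.5% | 29.9% | 27.5% | 54.9% | 45%, 50% |
| Same, three mediators in the model | 5% | 48.2% | 44.8% | 66.2% | 27%, 32% |
| | 2.5% | 29.9% | 27.0% | 54.1% | 45%, 50% |
| Same as first, 80 per arm | 5% | 60.8% | 56.8% | 77.7% | 22%, 27% |
| | 2.5% | 39.2% | 36.3% | 65.8% | 40%, 45% |
| d 0.5, slope 0.3 | 5% | 75.2% | 72.7% | 84.0% | 10%, 14% |
| | 2.5% | 59.7% | 57.5% | 75.1% | 21%, 24% |
| d 0.8, slope 0.3 | 5% | 98.3% | 98.0% | 99.3% | 1%, 1% |
| | 2.5% | 94.9% | 93.7% | 98.2% | 3%, 5% |
| d 0.3, slope 0.2 | 5% | 18.0% | 16.8% | 33.7% | 47%, 50% |
| | 2.5% | 7.9% | 7.8% | 23.6% | 67%, 67% |

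A separate run of the first scenario gave 50%, 47% and 70% at 5% alpha, and 29%, 27% and 58% at 2.5%. This accounts for the ranges quoted in the conclusion.

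**4. False positives.** With a = 0 and slope 0.2, rejection at nominal 5% was 1.4% (delta), 1.2% (bootstrapped SE) and 4.0% (percentile). At nominal 2.5% it was 0.4%, 0.4% and 2.0%. The highest percentile rates in the separate run were 4.7% and 2.6%.

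**The case against.** **The separate links are tested anyway.** A reader might infer that mediation is the whole of Aim 2, so that the trial would simply report no mediation. The documents do not support this. Section 2 states the Aim 2 hypotheses as two links, section 3.10.1 powers those links, and section 3.10.2 tests each one. In the first scenario both links are significant together in about 69% of trials at 5% and 56-57% at 2.5%, about as often as the percentile interval excludes zero. This limits the harm: the path results would sit beside a non-significant product test. It does not justify keeping the weaker product test, which would then often disagree with the paths it summarizes.

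**The loss depends on the effects and the alpha.** This stands. The figure of 45-50% needs 2.5%, which the article states only for Aim 1, and larger effects shrink the loss.

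**The authors may have meant bootstrap intervals.** This is possible in a condensed article, and the method references cited there were not available. But the text says standard errors. If intervals were meant, naming them settles the point.

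**The test is valid, only conservative.** True: its false-positive rate is below nominal. The objection is to power lost for no need.

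**Proportion mediated.** A reader might infer that this ratio is to be a headline result. Section 3.10.2 says only that it will be computed and does not rank it.

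**Conclusion.** The concern holds in conditional form. At the trial's own detectable effects (d about 0.5, standardized slope about 0.2, 210 participants in three arms), the stated tests have about 45-50% power for one indirect effect, against 67-70% for a percentile bootstrap interval, at 5% alpha. At 2.5% the figures are about 27-30% against 55-58%. The relative loss is about 30% and 45-50% respectively. It is about 10-25% at slope 0.3, a few percent when both paths are clearly larger, and greater when the flavor-to-mediator effect is smaller.

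This rests on a literal reading of bootstrapped standard errors, normal errors, mediators uncorrelated given flavor, and complete data on 70 per arm. The craving, withdrawal and negative-affect adjustments were not modeled.

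The Aim 1 analysis and the separate path tests of Aim 2 are untouched. Changing the test does not bring the indirect effect to 80% power at the design effects, because 80% on each link does not give 80% on their product.

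**What to change.** In section 3.10.2, replace the significance rule for the mediated paths with wording such as: *An indirect effect is declared present when the percentile bootstrap confidence interval for the product of the two coefficients, from at least 5,000 participant-level resamples and at the stated alpha, excludes zero.* State the Aim 2 alpha in the same place. Report each indirect effect in cigarettes per day with that interval. Give the proportion mediated as descriptive, with its own bootstrap interval, since a ratio to the total effect becomes unstable when that effect is small.

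The cost is a sentence or two and slightly more computation. Bootstrap resampling is already planned, and no further data or participants are needed. The downside is a false-positive rate close to nominal instead of far below it.
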